**Exclusion criteria (patients who meet any one of the following criteria will be excluded)**
Patients with insomnia caused by a variety of organic diseases or neurological or psychiatric disordersPregnant or lactating patients or those with a drug allergyPatients with more serious primary diseases such as cardiovascular and cerebrovascular diseases, gastrointestinal diseases, endocrine system diseases, or psychiatric disordersPatients with coagulation dysfunction and bleeding tendency

The baseline assessment will be performed by the same physician, and the results will be recorded in detail in the case report form. All participants will receive treatment for 4 weeks and undergo follow-up observation after treatment. The evaluation will be done at 3 time points: before treatment, after 4 weeks of treatment, and at 4 weeks after end of treatment. Each participant will receive a schedule of treatment dates and a schedule of follow-up appointments developed by research assistants who will be blinded to the grouping information.

In addition, all participants will be required to keep a sleep diary throughout the treatment and follow-up periods, recording the date of each insomnia episode, the length of time required to fall asleep, the number of times they wake up at night, the difficulty of falling asleep again, and the subjective feelings after waking up in the morning. Moreover, they will be asked to include sleep-related details as well as the name, dose, and time of use of other drugs (such as sleeping pills) during the trial and their own feelings after taking the drug.

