### Interventions

#### Overview

All participants will receive acupuncture based on the Jing Bie theory or conventional acupuncture at a frequency of 3 times a week. To ensure the accuracy and consistency of the treatment administered, all acupuncture physicians participating in this study are required to have passed the clinical standard operation training in this subject and have the corresponding professional qualifications. Moreover, any possible adverse reactions during the study will be recorded in detail.

During the study period, the use of any prescription or nonprescription drugs for insomnia will be prohibited in principle. Participants who are required to use drugs for other diseases, which may affect the central nervous system, or have a severe insomnia problem will be processed and recorded as a “significant program deviation” or “withdrawal from the study” event. For those who do need medication, their complete medication information will be included in the subsequent statistical analysis as a key covariate. All participants are required to maintain a relatively stable work and rest schedule during the study period and to record information such as their bedtime, wake-up time, and occurrence of night awakening in a daily sleep diary. The researchers will review the diary every week to identify and guide individuals who experience excessive daytime sleepiness (>1 h) or significant changes in work and rest schedule (>2 h). Such behavioral changes will be included as covariates in the analysis.

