### Sample Size and Statistical Methods

The main outcome measure of this study will be the total PSQI score at 4 weeks after treatment. The sample size was calculated on the basis of the expected difference between the test acupuncture group and the conventional acupuncture group in this index.

The expected effect size was determined as follows: studies have shown that acupuncture can significantly reduce PSQI scores compared with conventional therapy, with a combined mean difference of 2.0 to 3.5 points [16]. With reference to an RCT of similar design [17], we conservatively estimated that the mean difference (Δ) of PSQI between the 2 groups after treatment was 2.5 points, and the combined SD was approximately 4.0 points. According to this calculation, the standardized effect size is 0.625 (Δ/SD=2.5/4.0). Using G*Power software (version 3.1; Heinrich-Heine University Dusseldorf), setting α=.05 (bilateral) and test efficiency (1-β)=80%, according to a 1:1 distribution, the minimum sample size of each group was calculated to be 43. Considering a dropout rate of approximately 10%, 48 patients will be included in each group, and a total sample size of 96 patients was finally determined.

SPSS software (version 22.0; IBM Corp) will be used to analyze the collected data. All data will be expressed as mean (SD). For measurement data of the 2 groups, normally distributed data will be analyzed by independent 2-tailed *t* test and paired 2-tailed *t* test. If the data are not normally distributed, the Mann-Whitney rank sum test will be used. One-way ANOVA will be used for comparison between groups. Count data will be analyzed using a chi-square test, and rank data will be compared using the rank sum test and other analysis methods. A *P* value of ≤.05 will be considered statistically significant. To control for potential confounding, the use of concomitant medications and measures derived from sleep diaries will be incorporated as covariates into a generalized linear model for sensitivity analysis of the primary outcomes.

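### The sensitivity model for the primary outcomes adjusts for medication use and diary measures recorded after randomisation, so it cannot check the robustness of the total effect; the two sections on covariates also differ in scope

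*Protocol article*

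**What the plan says.** **Sample Size and Statistical Methods.** The two-group comparison is an independent t test, or a Mann-Whitney test if the data are not normal. Neither is adjusted. A further model follows, in which "the use of concomitant medications and measures derived from sleep diaries will be incorporated as covariates into a generalized linear model". The sentence goes on to call this a sensitivity analysis for the primary outcomes, and its stated purpose is control of confounding.

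**Interventions, Overview.** For patients who need medication, "their complete medication information will be included in the subsequent statistical analysis as a key covariate". Daytime sleepiness of more than 1 h and schedule shifts of more than 2 h, found at weekly diary review, are treated likewise: "Such behavioral changes will be included as covariates in the analysis". Neither sentence limits the covariates to a sensitivity analysis.

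**Participant Recruitment (text after Textbox 1).** The diary runs from treatment to the end of follow-up. It records "the length of time required to fall asleep, the number of times they wake up at night", difficulty in getting back to sleep, how the patient feels in the morning, and any other drugs taken, sleeping pills included.

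**Interventions, Overview, on medication.** Insomnia drugs are in principle not allowed. "Participants who are required to use drugs for other diseases, which may affect the central nervous system, or have a severe insomnia problem" are recorded either as a major deviation or as having left the study. No rule is given for choosing between the two.

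**The concern.** A confounder of the randomised comparison must be a cause of both the assigned arm and the outcome. With 1:1 random allocation (Randomization and Blinding), nothing that happens after allocation can be one. Medication taken during the trial and diary entries made during treatment come later. If the test acupuncture improves sleep more than the control acupuncture does, shorter latency, fewer awakenings and less use of sleeping pills are part of that improvement.

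Holding these variables equal between arms changes the question. It becomes how PSQI differs among patients whose diary sleep and medication use are the same. That is not the total effect that the trial is sized to detect. In addition, anything unmeasured that drives both the covariate and PSQI becomes associated with arm once the covariate is in the model, and the direction of that bias is not fixed.

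At stake is the only sensitivity analysis of the primary outcomes that the article describes. If it departs from the main test, readers will take the main result as fragile. If it agrees, they will take it as confirmed. Neither inference would be sound.

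**Working it through.** **1. The plan's own figure.** Inputs from Sample Size and Statistical Methods: "the mean difference (Δ) of PSQI between the 2 groups after treatment was 2.5 points", "the combined SD was approximately 4.0 points", and "setting α=.05 (bilateral) and test efficiency (1-β)=80" percent. The standardised effect is 2.5/4.0 = 0.625. The two-sample t test needs 41.17, that is 42 per group, against 43 stated. With 10% dropout, 43/0.90 = 47.8, that is 48. Power at 43 per group is 81.7%. The sample size is not in dispute.

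**2. Adding a covariate recorded after randomisation.** Let r be the within-arm correlation of the covariate with PSQI. Let dM be the treatment effect on the covariate in SD units, oriented so that treatment improves both. In a linear model with a common slope:

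- adjusted difference = 2.5 − r × 4.0 × dM
- residual SD = 4.0 × √(1 − r²)
- SE = residual SD × √(2/43) × √(1 + dM²/4)

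The documents give neither r nor dM, so both are assumptions, shown over a range. The top value of dM, 0.625, means that the covariate responds as strongly as PSQI is planned to.

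| r | dM | Adjusted difference | Share removed | Power of adjusted model, 43 per group |
|---|---|---|---|---|
| 0.3 | 0.3 | 2.5 − 0.36 = 2.14 | 14% | 72% |
| 0.5 | 0.5 | 2.5 − 1.00 = 1.50 | 40% | 49% |
| 0.7 | 0.625 | 2.5 − 1.75 = 0.75 | 70% | 21% |
| 0.3, 0.5, 0.7 | 0 | 2.50 | 0% | 85%, 91%, 98% |

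The last row is also the case for a baseline covariate: randomisation makes dM zero in expectation, so the effect is kept and precision improves.

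**3. Medication use driven by poor sleep.** This was simulated with assumed PSQI means of 8 and 10.5, SD 4, and a patient taking medication when PSQI plus noise (SD 2) exceeds 16, 14 or 12. Use is then 4% against 11% (test against control) at the first threshold, rising to 19% against 37% at the last. With a true difference of 2.5 and no effect of the drug on PSQI:

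- Adjusting for use gives 1.98, 1.67 and 1.40 points (21% to 44% removed).
- Leaving these patients out gives 2.05, 1.79 and 1.54 points (18% to 38% removed).
- Analysing everyone without adjustment gives 2.50.

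If the drug itself lowers PSQI by 2 points, the unadjusted difference among all patients is 2.35, 2.24 and 2.13. The adjusted figures stay at 1.98, 1.67 and 1.40, still below it.

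**4. The two sections side by side.** The statistical section confines the covariates to a sensitivity model. The Overview makes medication a key covariate in the later analysis, and behavioural change a covariate in the analysis, with no such limit. Both cannot be followed as written unless the Overview is taken to mean the sensitivity model only.

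**The case against.** The strongest reply is that this is a sensitivity analysis and nothing more. The main test is unadjusted, so under the statistical section the covariates take nothing from it. That stands. A reader might infer that the primary treatment effect itself is adjusted away, or that the trial's power falls to 21%. The documents do not support this: the power figures above belong to the adjusted model alone, and the protocol claims no power for that model.

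Second, the diary measures to be used are not listed. The only ones expressly named as covariates, daytime sleepiness and schedule shifts, are not near-duplicates of PSQI, and both arms receive active acupuncture. This also stands, and it is why the size is given as a range that includes zero. It does not rescue the rationale, since the named measures are recorded after randomisation too.

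Third, Table 1 ticks medication at week 0 only, so baseline medication might be meant. The Overview does not read that way: it concerns patients who come to need drugs during the study.

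Fourth, confounding is a fair concern for the non-randomised healthy group. Randomization and Blinding deals with that comparison separately, and the model at issue is for the primary outcomes.

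On withdrawal, a reader might infer that treatment failures are removed from the trial. The Overview speaks of a severe insomnia problem, not of worsening. It offers two ways of recording it, and patients recorded as deviations can still supply their medication data. The article does not say that outcomes of those who leave go uncollected or are excluded. The 4 withdrawals among 40 enrolled are reported without arm or reason and settle nothing.

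**Conclusion.** The concern holds for the sensitivity model. Medication use and diary measures recorded after randomisation are not confounders of the randomised comparison. If treatment changes them, the adjusted model estimates a different quantity and cannot show whether the total effect is robust. With r of 0.3 to 0.7 and dM of 0.3 to 0.625, both assumed, the adjusted difference would be 2.14 down to 0.75 points against the planned 2.5. With dM of zero nothing is removed. These sums describe the part of the effect that is blocked; bias from unmeasured common causes could go either way, so a shift towards no difference is not guaranteed.

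The main t test or Mann-Whitney test is unaffected, unless the Overview is read as putting the covariates into it. The two sections need to be reconciled for that reason.

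Bias in the main test through withdrawal is conditional: it arises only if outcomes of patients who take medication or sleep badly are not collected or are excluded.

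**What to change.** 1. Remove medication use and diary measures recorded after randomisation as covariates from every model of the randomised comparison, and drop confounding as the reason.
2. Limit covariates to values recorded before randomisation, for example baseline PSQI and baseline medication status. Table 1 already collects both at week 0.
3. Report on-study medication use and diary measures by arm, as outcomes.
4. Reconcile the Interventions Overview with the statistical section, so that both state the same covariates and the same role for them.
5. In the Overview, separate stopping study treatment from leaving the study. Continue to collect PSQI where the patient agrees, and analyse patients as randomised. The clinical rule on medication and withdrawal is for the sponsor to reconcile.

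The cost is a change of wording and some added follow-up of patients who stop treatment. The sample size of 48 per group is unchanged. Recruitment is due to run to the end of 2026, so the change can still be made before any analysis.

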### Final Report and Publication

After the end of the study, the main researchers will take the lead to cooperate with the researchers at each clinical department to write the research summary report, and the researchers at each clinical department will sign the research summary report. The research report will include a description of the research purpose, the methods used in the research, and the results and conclusions.

## Results

This study was funded in November 2023. Recruitment and data collection began in January 2024. The results will be shared with participants, researchers, and the public via conferences, publications, and online platforms. The findings will be submitted to a peer-reviewed journal. Participant recruitment is underway and will continue until the target sample size of 96 patients with primary insomnia of liver depression and spleen deficiency type and 48 healthy controls is reached. Participant recruitment is scheduled to be completed by the end of 2026. Each enrolled patient will undergo the 4-week intervention followed by a 4-week follow-up period as per the study protocol. As of December 2025, a total of 40 participants have been enrolled, of whom 4 have withdrawn. Data collection is expected to conclude by the end of 2026, with full data analysis and manuscript preparation completed by summer 2027.

## Discussion

### Study Rationale

In this study, an RCT was designed to evaluate the efficacy of acupuncture at specific meridians and the acupoints SI17 and TE16 on patients with primary insomnia of liver depression and spleen deficiency type and to conduct a parallel assessment of ANS regulation using HRV and neurochemical indicators.

The selection of the cervical acupoints SI17 and TE16 is based on the classical meridian divergence (Jing Bie) theory of TCM [5]. According to “Lingshu · Jing Bie,” although SI17 belongs to the small intestine meridian, it is located at the intersection of the liver and gallbladder meridians. Therefore, acupuncture at SI17 can soothe and regulate the liver and gallbladder qi. Although TE16 belongs to the triple energizer meridian, it is located at the intersection of the triple energizer, pericardium, and gallbladder meridians. Acupuncture at TE16 can regulate the qi of the Shaoyang meridian, relieve the stagnation of the upper energizer and tranquilize the mind, and provide a theoretical basis for related diseases. In TCM, the neck is a key region where multiple yang meridians converge [18]. As pivotal acupoints in the neck, SI17 and TE16 are essential for regulating the mind and balancing yin and yang, and their clinical values stem from the deep regulation of ying-wei qi and blood by the hand Taiyang and hand Shaoyang meridians. Specifically, the Tianrong point follows the path of “entering the armpit and walking the heart” by the hand Taiyang meridian, which has the effect of dredging the neck qi and blood and calming the heart and nerves. Its anatomical deep layer corresponds to the cervical sympathetic ganglion, which can inhibit the excessive excitement of the sympathetic nerve. The Tianyou acupoint, with the function of the hand Shaoyang meridian “scattered in the chest,” can regulate the triple energizer qi, straighten out the upper energizer, and affect the activity of the vagus nerve. According to the “Lingshu · Jing Bie,” these divergences “branch from the main channels, enter the body cavity, link exterior and interior, and harmonize *ying* (nutritive) and *wei* (defensive) energies.” The yang meridians are different from the original meridians, and the yin meridians are different from the yang meridians in the exterior and interior, which strengthens the close relationship between the limbs and the zang-fu organs, head, and face. In TCM, insomnia of the liver depression and spleen deficiency type is considered to stem from disrupted qi flow and impaired balance between ying and wei [19,20]. The mechanism of acupuncture involves regulating the relationship between yin and yang, the unity of opposites, to restore the harmonious flow and balance of qi in the whole body [21]. On the basis of this principle, specific acupoints on the neck are stimulated to dredge the Shaoyang meridian and reconcile ying and wei so as to promote yang qi into yin and support natural sleep. This follows the classical TCM principle that “acupuncture treats areas along the pathway of the meridian.”

Notably, this traditional rationale aligns with modern neuroanatomical insights. The cervical regions where these meridian divergences run are anatomically close to major sympathetic ganglia, such as the stellate ganglion [22,23]. Therefore, acupuncture at SI17 and TE16 may modulate local sympathetic nerve activity, in a way similar to SGB—a procedure known to influence autonomic function [24-26]. This integrated view connects the TCM concepts of qi regulation and ying*-*wei harmony with the modern understanding of ANS balance, offering a coherent mechanistic framework for acupuncture.

### Proposed Mechanism and Empirical Testing

The proposed mechanism can be traced through specific physiological pathways. The anatomical proximity of these points to the cervical sympathetic chain means that stimulation may send signals through the spinal cord to higher brain regions that regulate autonomic function, such as the brain stem and hypothalamus [27,28]. This influence on the central nervous system can rebalance the sympathetic and parasympathetic activity, a change measurable through HRV [29-32]. Thus, HRV provides an objective link between the TCM idea of restored ying-wei harmony and modern metrics of ANS balance. Beyond this neural pathway, the intervention likely also involves neuroendocrine adjustments [33-35]. Chronic insomnia and the TCM pattern of liver qi stagnation are both associated with overactivity of the body’s stress response system, the hypothalamic-pituitary-adrenal axis [36-38]. By mitigating excessive sympathetic drive, acupuncture may help calm the hypothalamic-pituitary-adrenal axis hyperactivity [39], potentially leading to lower cortisol levels and a more sleep-conducive internal milieu [40-42]. In summary, the treatment is hypothesized to work through a convergent network, modulating both neural excitability and endocrine function to address the multifaceted pathophysiology of insomnia.

To empirically test this mechanistic model, our study employs a multimethod assessment strategy. In addition to standard patient-reported outcomes (PSQI and ISI), we will measure HRV to directly quantify ANS changes [43]. We will also analyze the levels of key neurotransmitters—GABA and Glu. We hypothesize that successful treatment will be correlated with a shift toward a less excited central nervous system state, reflected in an increased GABA to glutamate ratio [18]. This combined biochemical and physiological evidence aims to clarify how stimulation at these specific points translates into clinical improvement, thereby strengthening the scientific rationale for this targeted acupuncture protocol.

This study incorporates a parallel cohort of healthy controls to establish normative baselines for HRV and relevant neurochemical markers. These reference values will enable the quantitative assessment of the severity of ANS dysfunction in patients with insomnia and provide a benchmark for evaluating postintervention recovery. This comparative design strengthens the robustness of the findings and supports a multidimensional evaluation of treatment efficacy.

To comprehensively capture both objective and subjective dimensions of sleep and autonomic function, the primary outcome indicators include the PSQI and SF-36. The secondary outcome indicators include the ISI and DBAS-16 as well as GABA and Glu levels. These 2 neurotransmitters were selected as biomarkers because they play an important role in sleep-wake regulation and the high arousal state characterized by primary insomnia. Assessing these neurochemicals will help to elucidate the mechanisms underlying treatment response.

Methodologically, the trial employs a single-blind, randomized design with block randomization to minimize selection bias. The sample size was determined by an a priori power calculation to ensure adequate statistical power, and all acupuncture procedures will be performed adhering to a strict standardized protocol to maintain treatment fidelity across participants. Focusing exclusively on patients with the liver depression-spleen deficiency pattern will reduce clinical heterogeneity, allowing a more precise investigation of acupuncture mechanisms within this defined TCM syndrome framework.

### Limitations

Several limitations warrant consideration. Achieving complete blinding in acupuncture trials remains inherently challenging, and the participant age range (18‐40 y) may constrain the generalizability of the findings to older populations. Nevertheless, the protocol aligns with the CONSORT (Consolidated Standards of Reporting Trials) guidelines through structured data collection, systematic adverse event monitoring, and prespecified statistical analysis—features that collectively uphold the internal validity and interpretability of the study outcomes.

This study has some limitations. First, the scope of sample selection is limited. The inclusion criteria limited participant age to 18 to 40 years and the course of the disease to more than 2 weeks. Although a narrow age range is conducive to controlling confounding age factors, it cannot represent the situation of patients with insomnia in other age groups, which limits the universality of the research results and may lead to age-related bias in the conclusions. Second, there are limitations in the blinding design. Due to the significant difference between the intervention strategies of the Jing Bie theory acupuncture group and the traditional acupuncture group, the blinding protocol for acupuncture physicians faces challenges in practice. Therefore, this study adopts a single-blind design. Although this may, in theory, introduce operator bias, several measures will be taken to maintain methodological rigor: the acupuncture physician will follow strict standardized operating procedures; the outcome evaluators and data analysts will remain blinded to the grouping; and the participants will know only that they received active acupuncture intervention and will not know the specific grouping. These measures aim to minimize potential bias while maintaining the authenticity of clinical practice. Future studies may consider using sham acupuncture or noninvasive needles in the control group to achieve double blinding, although such methods also have inherent limitations in simulating real acupuncture effects.

In summary, this study will explore a new path for acupuncture treatment of insomnia based on the theory of Jing Bie and establish acupoint selection (targeting cervical regions to regulate autonomic function) and evaluation (integrated comprehensive evaluation program using PSQI, HRV, and neurochemical biomarkers), providing a reference for subsequent research. However, the limitations of sample representativeness and blinding design suggest that future research needs to be improved in terms of expanding the age range of the sample and optimizing the strategy of implementation of blinding, so as to further verify and expand the findings of this study.

